## Abstract

**Introduction:**

Use of the prehospital 12-lead ECG (PHECG) is recommended in patients presenting to emergency medical services (EMS) with suspected acute coronary syndrome (ACS). Prior research found that although PHECG use was associated with improved 30-day survival, a third of patients (typically women, the elderly and those with comorbidities) under EMS care did not receive a PHECG.

The overall aim of the PHECG2 study is to update evidence on care and outcomes for patients eligible for PHECG, specifically addressing the following research questions: (1) Is there a difference in 30-day mortality, and in reperfusion rate, between those who do and those who do not receive PHECG? (2) Has the proportion of eligible patients who receive PHECG changed since the introduction of primary percutaneous coronary intervention networks? (3) Are patients that receive PHECG different from those that do not in terms of social and demographic factors, or prehospital clinical presentation? (4) What factors influence EMS clinicians’ decisions to perform PHECG?

**Methods and analysis:**

This is an explanatory, mixed-method study comprising four work packages (WPs). WP1 is a population-based, linked-data analysis of a national ACS registry (Myocardial Ischaemia National Audit Project). WP2 is a retrospective chart review of patient records from three large regional EMS. WP3 comprises focus groups of EMS personnel. WP4 will synthesise findings from WP1–3 to inform the development of an intervention to increase PHECG uptake.

**Ethics and dissemination:**

The study has been approved by the London-Hampstead Research Ethics Committee (ref: 18LO1679). Findings will be disseminated through feedback to participating EMS, conference presentations and publication in peer-reviewed journals.

**Trial registration number:**

NCT03699137

Key questionsThe prehospital 12-lead ECG (PHECG) is associated with better survival in patients with acute coronary syndrome (ACS), but is potentially underused.In this study, we will examine whether the proportion of patients who receive PHECG has changed in the primary percutaneous coronary intervention era. In addition, we will look at barriers and facilitators of PHECG use in terms of patient-related factors and emergency medical services personnel perspectives.Findings from this study will provide an insight into PHECG use in patients with ACS and allow the development and testing, in a randomised trial, of an intervention to improve uptake.

## Introduction

The performance of a 12-lead ECG is recommended in the assessment of patients with suspected acute coronary syndrome (ACS) presenting in the community to emergency medical services (EMS).^1–3^ A prehospital 12-lead ECG (PHECG) informs decision-making in three components of immediate care: targeted prehospital treatment, transport to an appropriate receiving hospital and provision of information required to activate a response from the receiving cardiac catheter laboratory when ST-segment elevation myocardial infarction (STEMI) is suspected.^4^

This study builds on our previous research, which reported an association between PHECG and lower short-term mortality following STEMI and non-STEMI (30-day mortality 7.4% vs 8.2%, OR 0.94, 95% CI 0.91 to 0.96).^5^ Earlier research focused on the association of PHECG with process-of-care quality descriptors such as ‘call-to-reperfusion’ time.^6 7^ A subsequent systematic review and meta-analysis has confirmed the association of PHECG with improved clinical outcomes,^8^ and this evidence has been incorporated into international guidelines and quality indicators for prehospital care of patients with ACS.^2 3^ However, we found PHECG was underused, particularly in older patients, women and people with comorbidities.^5^

We showed that women were less likely to receive PHECG than men (OR 0.87, 95% CI 0.86 to 0.89),^5^ and suggested that this may be because the majority of EMS personnel at that time were male. The lower rate of PHECG in women was also reported from the national SWEDEHEART (The Swedish Web-system for Enhancement and Development of Evidence-based care in Heart disease Evaluated According to Recommended Therapies) registry (OR 0.89, 95% CI 0.87 to 0.92),^9^ though these authors offered a different explanation related to ‘uncontrolled confounding of presenting symptoms and type of myocardial infarction’. A systematic review reported that women are less likely to present with chest pain and more likely to have prior heart failure, which may ‘mask’ the true diagnosis.^10^

Emergency situations force clinicians into a reliance on past experiences,^11 12^ intuition and personal decision rules (‘rules of thumb’),^13^ even though these approaches are potential sources of error and bias.^14^ In prehospital emergency care, suggested influences on clinical decisions include a desire to ‘cover one’s back’,^15^ pragmatism (busy shift or end of a shift)^16^ and multilevel system influences.^17^

Since our earlier study there has been significant change in reperfusion strategies for STEMI in the UK, with primary percutaneous coronary intervention (pPCI) superseding fibrinolytic treatment as the treatment of choice.^18^ This has required changes in EMS organisation and practice, including direct transportation to pPCI-capable hospitals and the atrophy of existing programmes of prehospital administration of thrombolytic treatment by ambulance paramedics.

Considering this major change in practice and an increased emphasis on PHECG in guidelines, we expected there to be an increase in the use of PHECG since our first report. On the contrary, it appears to have declined to 64% for STEMI and 44% for non-STEMI, respectively, in 2015–2016 (National Institute for Cardiovascular Outcomes Research (NICOR), personal communication). It is therefore timely to update our analysis on a more recent cohort of patients and to explore potential determinants of why PHECG is/is not recorded.

Our a priori hypotheses are:

PHECG use by EMS personnel is associated with more timely processes of care and a lower short-term mortality rate in patients with suspected ACS, for both STEMI and non-STEMI cases.Patients who do not receive a PHECG systematically differ from those who do.EMS clinician decision-making regarding PHECG is influenced by more than clinical (pathophysiological) characteristics.It is possible to use the findings from this study as the first stage of the development and subsequent evaluation of a complex intervention^19^ designed to improve the uptake of PHECG.

Our research questions (with their respective work packages (WP)) are:

For patients presenting to EMS with suspected ACS, is there a difference in 30-day mortality and reperfusion strategy in patients managed outside hospital by EMS between those who do and those who do not receive a PHECG? (WP1)Has the proportion of eligible patients who received a PHECG changed since the national rollout of pPCI networks? (WP1)Are patients that receive a PHECG different from those that do not in terms of social and demographic factors, and in their prehospital clinical presentation? (WP2)What factors do EMS clinicians report as influencing their decision to perform a PHECG? (WP3)

## Methods and analysis

To answer our research questions an explanatory, mixed-method study will be undertaken,^20^ in which the qualitative data will be used to aid understanding of the quantitative findings, consisting of the following four WPs:

*WP1—population-based, linked cohort study using Myocardial Ischaemia National Audit Project (MINAP) data from 2010 to 2017* to update evidence on care and outcomes for patients eligible for PHECG. MINAP is a comprehensive registry of ACS hospitalisations mandated by the Department of Health. Each MINAP entry provides patient demographic and clinical details of the patient journey across 122 data items. Data collection and management have been described previously.^21^

*WP2—retrospective chart review*^22^*of EMS records* to collect data on factors recorded by EMS staff that may be associated with PHECG use, but are not routinely collected in MINAP.

WP3—EMS clinician self-report on PHECG recording, using focus groups.

*WP4—synthesis of the findings from WP1, WP2 and WP3*. This will be conducted to address our research questions, within our aim of using qualitative findings as explanatory of quantitative results^20^ and with the understanding that these data are intended as the development phase for the design of a complex intervention for further testing.^19^

### Study setting

WP1 will use existing data from MINAP, covering England, Wales and Northern Ireland.

For WP2 and WP3, data will be collected at three participating EMS in England and Wales.

### Study population

WP1: patients will be eligible for the study if aged 18 years or older when attended by EMS and admitted with ACS between 1 January 2010 and 31 December 2017 to one of 228 participating hospitals in England, Wales and Northern Ireland mandated to enter data into MINAP. For patients with multiple admissions, only the earliest record of their ACS event in MINAP will be used.

MINAP is overseen by a multiprofessional Domain Expert Group of stakeholders within the National Cardiac Audit Programme (NCAP). As such, this study will include data collected on behalf of the British Cardiovascular Society under the auspices of NCAP, in which patient identity is protected.^21^

WP2 will include a stratified random sample of patients with suspected ACS (by initial diagnosis in MINAP) attended by one of the three participating EMS during the study period. It will include those with or without PHECG.

WP3 will include a purposive sample of EMS clinicians of different clinical grades, with varying levels of experience in caring for patients with ACS in the prehospital setting, who are trained in the use of PHECGs and employed by one of the three participating EMS.

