### Data collection

WP1: we will use existing MINAP registry data, collected prospectively at each hospital using a secure electronic system, encrypted and transferred online to a central database in which patient identity is protected.^21^ We will link MINAP data to ONS Civil Registry mortality data at individual level through NHS Digital.

WP2: we will randomly select a cohort of patients with and without PHECG, with ACS recorded in MINAP, for the three participating EMS using a unique identifier for patients in MINAP who came to hospital via EMS. The sample will be stratified by preagreed demographic variables (such as sex and age band) to ensure it is sufficiently representative. We will report key characteristics of the sample, those of the MINAP ACS subpopulation (those who came via EMS), and the overall MINAP population.

We will employ and train paramedic researchers at each site to retrieve and extract data from the EMS records of each sampled patient. We will collect data on factors that may influence the use of a PHECG which are not recorded in MINAP, including coded data on patient symptoms, prehospital diagnosis of ACS, EMS clinician training level and sex, patient refusal, patient ethnicity, language spoken, capacity to communicate and/or consent. The paramedic researchers will extract relevant narrative data from the ‘free-text’ section within EMS records. A second researcher will independently extract data for a random sample of 10% of the cases for quality assurance purposes.

WP3—we will conduct focus groups using a semistructured approach, aiming to explore the views of EMS clinicians about the role of PHECG, experiences of assessing patients with STEMI and non-STEMI, and influences on whether or not to record a PHECG. A topic guide will be constructed in the context of the quantitative findings and with input from EMS clinicians, patient and public representatives, and in the context of literature that highlights complexity and multiple influences on decisions made in the EMS setting. Focus group discussions will be digitally recorded and transcribed verbatim. Participants will be briefed at recruitment and at the beginning of each focus group not to disclose any information that might serve to identify individual(s).

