### Analysis

WP1—available demographic data will be presented using interval categories for continuous variables where appropriate. We will present mortality as (1) the proportion occurring within 30 days of hospitalisation, and (2) time to death, summarised using Kaplan-Meier survival curves. We will estimate (with 95% CIs) the outcomes associated with the performance of PHECG via a binary variable, adjusting for other statistically significant demographic and clinical variables.

A similar modelling approach will be used for other categorical variables of interest (for instance, use of reperfusion); natural extensions within the framework of generalised linear models will cover both the analysis of any counts and measurement outcomes of interest.

WP2—partitioning our sample of ACS cases by PHECG or not, we will use univariate and multivariate analyses to explore differences in patient symptoms and other factors between these two groups; we will report and explore differences across stratifying variables (such as age band, sex), and across categorisations emerging from consideration of free-text narratives in EMS records). We will use binary logistic regression to explore the extent to which factors are associated with PHECG use or not in ACS cases, reporting odds ratios (with 95% CIs) for statistically significant variables. Inter-rater reliability of data retrieval will be assessed using Cohen’s kappa.

WP3—focus group transcripts will be managed using NVivo software.^24^ Initially, we will conduct an inductive thematic analysis, using bracketing, and with iteration to the coding framework based on deep reading of the data, discussion within the research team and member checking. We will then use framework analysis^23^ and analyse whether the generated themes show consensus or dissent when considered against any differences in the characteristics of the focus group participants (eg, grade of EMS clinician, local practice). At least two researchers will read, reread and draft a coding framework for discussion and blinded application to at least two transcripts. The coding framework will be developed iteratively by discussion throughout the analysis process. Researchers involved in the qualitative data collection and analysis will meet regularly to reflect on their assumptions, personal influences and data interpretations.

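### WP1 uses only the earliest MINAP record of the event, so reperfusion given after transfer may be missed, probably more often in patients without PHECG

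*Protocol article*

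**What the plan says.** The record-selection rule stands in the Protocol article, Study population, WP1: "For patients with multiple admissions, only the earliest record of their ACS event in MINAP will be used". It makes no exception for outcomes.

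Reperfusion is compared by exposure in WP1. The Abstract asks: "Is there a difference in 30-day mortality, and in reperfusion rate, between those who do and those who do not receive PHECG". The Introduction puts the same question in terms of strategy: "is there a difference in 30-day mortality and reperfusion strategy in patients managed outside hospital by EMS". The Analysis section adds: "A similar modelling approach will be used for other categorical variables of interest (for instance, use of reperfusion". Main outcome measures lists only 30-day mortality and the proportion with PHECG over time for WP1, so reperfusion belongs to research question 1 without being a listed main outcome.

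On the data source, Methods and analysis calls MINAP a registry of hospitalisations for ACS. Data collection says its data are "collected prospectively at each hospital using a secure electronic system". The only external linkage named is to ONS mortality data. Inter-hospital transfer is not mentioned anywhere.

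On the link between exposure and hospital, the Introduction says that a PHECG informs three parts of immediate care, among them "transport to an appropriate receiving hospital and provision of information required to activate a response from the receiving cardiac catheter laboratory". It also says that the move to primary PCI (pPCI) brought "direct transportation to pPCI-capable hospitals".

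**The concern.** The earliest record is the natural place to fix the index event, the exposure and the baseline. Reperfusion is different, because it can be given later in the same event and at another hospital. A patient whose PHECG points to STEMI may go straight to a pPCI centre, and the first record then holds the treatment. A patient without a PHECG may arrive first at a hospital that does not offer pPCI, be diagnosed there and be transferred. If the treatment is then recorded only by the second hospital, the rule discards it.

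The error would run in one direction, since reperfusion can be missed but not invented, and its frequency would probably depend on the exposure. That is differential outcome misclassification in a comparison named in research question 1. Covariate adjustment cannot repair it, because the outcome data are no longer in the analysis set. A very large sample makes the biased estimate precise without making it correct.

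**Working it through.** **Step 1: what the text settles.**
- One record per patient is used in WP1, the earliest (Study population).
- Records are made hospital by hospital (Data collection).
- Reperfusion has no named source outside MINAP. Mortality has one, ONS.
- PHECG informs the choice of receiving hospital, and pPCI is tied to certain hospitals (Introduction).

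**Step 2: what the text leaves open.**
- Whether a transfer produces a second MINAP record.
- Whether the first hospital's record also holds reperfusion given elsewhere. Methods and analysis describes an entry as following the patient's course of care in 122 items, which is compatible with either answer.
- How often patients with and without PHECG are transferred, and how often they are reperfused. No figure is given, so there is no stated figure to reproduce.

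**Step 3: illustration.** Let R be the true reperfusion proportion, equal in both groups, so that the true odds ratio (OR) is 1. Let m1 (PHECG) and m0 (no PHECG) be the shares of reperfused patients whose treatment appears only in a later record. Then:

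- recorded rates: a = R(1 − m1) with PHECG, b = R(1 − m0) without
- recorded OR = [a/(1 − a)] / [b/(1 − b)]

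In the lower four rows, m is built as (share going first to a non-pPCI hospital) × (share of their reperfusions found only in the second record). All values of R, m1 and m0 are assumptions; none is in the article.

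| R | m1 | m0 | Recorded rates | OR |
|---|---|---|---|---|
| 75% | 0 | 0 | 75% vs 75% | 1.00 |
| 75% | 5% | 5% | 71.25% vs 71.25% | 1.00 |
| 75% | 2% | 5% | 73.5% vs 71.25% | 1.12 |
| 75% | 2% | 10% | 73.5% vs 67.5% | 1.34 |
| 80% | 5% × 25% = 1.25% | 20% × 25% = 5% | 79% vs 76% | 1.19 |
| 80% | 5% × 50% = 2.5% | 40% × 50% = 20% | 78% vs 64% | 1.99 |
| 70% | 1.25% | 5% | 69.1% vs 66.5% | 1.13 |
| 70% | 2.5% | 20% | 68.25% vs 56% | 1.69 |

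For the sixth row: (0.78/0.22) / (0.64/0.36) = 3.545 / 1.778 = 1.99.

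**Step 4: would chance hide it?** Estimated sample size anticipates over 500 000 cases in WP1. Borrowing the 2:1 ratio of PHECG to no PHECG stated for WP2, and R = 75%, the 95% CI half-width for a difference in proportions is 1.96 × √[0.75 × 0.25 × (1/333 333 + 1/166 667)] = 0.0025, or 0.25 percentage points. If only 100 000 cases were relevant to reperfusion, it would be 0.57 points. The mildest differential row at R = 75% (2% vs 5%) gives a false difference of 73.5 − 71.25 = 2.25 points, well outside either.

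**The case against.** The strongest case against is that the harm needs two facts the article does not state: that a transfer creates a separate record, and that the first record omits later treatment. The description of an entry as following the patient's course leaves room for the first record to be complete, in which case there is no bias. This stands, and the point must be conditional.

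Second, the rule may be aimed at repeat ACS admissions over eight years, so that each patient contributes one event. That reading is reasonable, but it does not remove the problem: under an earliest-record rule a transfer record is still a later record and is not used. The sentence also speaks of the earliest record of the event, not of the earliest event.

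Third, a reader might infer that PHECG decides the hospital and that the losses fall mostly on patients without PHECG. The documents do not support that strength. The Introduction says only that PHECG informs the decision, it does not say where patients without PHECG are taken, and no transfer figures are given. A greater loss without PHECG is a plausible inference, no more.

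Fourth, reperfusion is not a listed main outcome measure, and 30-day mortality is untouched by this route. Both are correct and limit the scope.

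Fifth, record joining commonly sits in a full protocol or SAP. Silence on it would be no finding. Here, however, the article states a single-record rule without exception, and that rule needs amending.

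**Conclusion.** The point holds conditionally. WP1 fixes a one-record rule and then compares reperfusion by PHECG status with no other named source. If the first record lacks reperfusion given after transfer, affected patients are misclassified, probably more often without PHECG, and the comparison is biased in favour of PHECG.

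A reader might go further and infer that reperfusion is in fact lost and that the planned result will be inflated. The documents establish neither. The size is unknown: the spurious OR is 1.00 if nothing is lost or the loss is equal (given a true OR of 1), 1.13 to 1.69 at 70% true reperfusion and 1.19 to 1.99 at 80% under the assumed routing and loss. The upper end rests on a fifth of reperfusions being missed without PHECG, which is an assumption.

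The amendment is worth making because it is cheap, does little harm if the first record proves complete, and guards against a bias that neither adjustment nor sample size can remove.

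**What to change.** In Study population (WP1), limit the earliest-record rule to the index event, the exposure and the baseline variables. Add to Analysis (WP1) that:

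- reperfusion (any, type and time) is ascertained from all MINAP records of the same patient that belong to the index event, joined within a transfer window fixed before the data are examined;
- reperfusion from the first record alone is reported as a sensitivity analysis;
- the share of patients transferred is reported by PHECG status.

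If the first hospital's record already holds treatment given after transfer, the article should say so. The two analyses should then agree closely.

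Cost: a short change of wording and a record-joining step in data preparation. No new data source is needed, since applying the present rule already requires identifying a patient's several records. The drawback is that a few new events inside the window may be merged with the index event.

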### Main outcome measures

WP1—all-cause 30-day mortality (the proportion of patients who die from any cause within 30 days of the date of their event) calculated from linked MINAP and Office for National Statistics (ONS, Civil Registry) mortality data.

Proportion of eligible patients for whom PHECG performed over time.

WP2—factors that may influence the use of PHECG in ACS (eg, patient symptoms, prehospital diagnosis, recognition of ACS, EMS clinician training level and gender, patient refusal, patient ethnicity, language spoken, capacity to communicate and/or consent).

WP3—an understanding of influences on clinical decision-making regarding recording of the PHECG in ACS (and thereby, potential explanations of quantitatively measured rates of PHECG use).

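### Keeping only each patient's earliest record suits 30-day mortality, but it can distort the 2010–2017 trend in prehospital ECG use because repeat patients drop out progressively

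*Protocol article*

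**What the plan says.** The Study population section of the protocol article sets one selection rule for the whole of work package 1 (WP1): "For patients with multiple admissions, only the earliest record of their ACS event in MINAP will be used". Eligible patients are those attended by EMS and "admitted with ACS between 1 January 2010 and 31 December 2017". The Methods and analysis section likewise describes WP1 as a "linked cohort study using Myocardial Ischaemia National Audit Project (MINAP) data from 2010 to 2017".

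WP1 answers two different questions. The first concerns 30-day mortality and reperfusion with and without PHECG. The second, in the Introduction, is: "Has the proportion of eligible patients who received a PHECG changed since the national rollout of pPCI networks". Main outcome measures lists the matching outcome: "Proportion of eligible patients for whom PHECG performed over time". The article makes no exception to the record rule for this second question.

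The Introduction also reports from the team's earlier work that "we found PHECG was underused, particularly in older patients, women and people with comorbidities".

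**The concern.** One record per patient is a natural choice for 30-day death: patients are independent and each contributes one outcome. A calendar trend needs something else, namely that each year's denominator is formed in the same way. Under the earliest-record rule it is not.

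With data from 2010 to 2017, a 2010 record can be removed only because the same patient was admitted earlier in 2010. A 2017 record is also removed if the patient was admitted in any of the seven preceding years. Patients with an earlier ACS are therefore well represented in 2010 and increasingly scarce by 2017.

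If PHECG use differs between first and repeat admissions, the yearly proportion moves because the mix of patients moves. Repeat patients plausibly carry more comorbidity, a group in which the earlier work found PHECG underused. If so, the retained cohort becomes more likely to receive PHECG each year, and part of any real decline would be masked. A large sample does not help: it narrows the interval but leaves this shift in place.

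**Working it through.** The article gives no figure for the PHECG trend, so there is none to reproduce. Its only power statement concerns WP2 and has no bearing here.

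**Inputs from the document.** Eight calendar years; over 500 000 expected cases (Estimated sample size), so 500 000 / 8 = 62 500 a year if spread evenly; PHECG use of 64% in STEMI and 44% in non-STEMI in 2015–2016 (Introduction).

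**Assumed inputs, not in the document.** Repeat-ACS risk *h1* in the first year and *h2* a year after that, at a low setting (6%, 1.5%) and a high setting (10%, 3%); 7% yearly attrition; 15 years of history; and a gap *g*, PHECG use in first minus repeat admissions, constant over time.

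**Step 1: the artefact.** If practice is constant, the observed proportion in year *t* is p(first) − g × s(t), where s(t) is the share of retained records with an earlier ACS admission. The spurious change is therefore g × [s(2010) − s(2017)].

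**Step 2: the repeat share.** Take one unit of first-ever admissions a year. The repeat rate at lag *k* years is r(0) = h1/2, r(1) = (h1 + h2)/2 and r(k) = h2 for k = 2 to 15, each multiplied by 0.93^k.

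- All admissions: R = sum over k = 0 to 15; share = R/(1 + R), the same in every year.
- Earliest in window, year *t* (2010 is t = 0): K(t) = (1 − h2)^t × sum over k = t+1 to 15; share = K/(1 + K).

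The sum of 0.93^k is 7.882 for k = 2 to 15 and 3.521 for k = 8 to 15.

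- Low: R = 0.0300 + 0.0349 + 0.1182 = 0.1831, share 15.5%. K(2010) = 0.0349 + 0.1182 = 0.1531, share 13.3%. K(2017) = 0.985^7 × 0.015 × 3.521 = 0.0475, share 4.5%.
- High: R = 0.0500 + 0.0604 + 0.2365 = 0.3469, share 25.8%. K(2010) = 0.0604 + 0.2365 = 0.2969, share 22.9%. K(2017) = 0.97^7 × 0.03 × 3.521 = 0.0853, share 7.9%.

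**Step 3: the shift** (falls taken before rounding).

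| Setting | Fall in repeat share | g = 5 points | g = 10 points | g = 0 | g = −5 points |
|---|---|---|---|---|---|
| Low | 8.7 points | +0.44 | +0.87 | 0 | −0.44 |
| High | 15.0 points | +0.75 | +1.50 | 0 | −0.75 |

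A second cohort simulation (50,000 new patients a year, 25-year burn-in, risk 6% to 10% in year 1 and 2% to 3% a year after) agrees. The repeat share falls from 19.6% to 10.1%, or from 27.4% to 13.4%, giving 9.5 × 0.05 = 0.48 to 14.0 × 0.10 = 1.40 points. A wider grid (share falling 5 to 20 points, gap 2 to 15 points) runs from 5 × 0.02 = 0.1 to 20 × 0.15 = 3.0 points.

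**Step 4: sampling error.** For a difference between two years at p = 0.55, SE = sqrt(2 × 0.55 × 0.45 / 62 500) = 0.28 points and the 95% half-width is 1.96 × 0.28 = 0.55 points. At p = 0.60 the half-width is 0.54.

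**Step 5: comparison.** The low end (0.44) lies inside the half-width. The high end (1.50) is about 2.7 times it (1.50 / 0.55).

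**The case against.** Four arguments weigh against the point.

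- **Sign.** No passage reports PHECG use in patients with a prior ACS. What the Introduction reports concerns age, sex and comorbidity. A known cardiac history could help crews recognise ACS and so raise PHECG use. This stands: the direction is an inference, and the model shows it reversing.
- **Reading of the rule.** The text says earliest in MINAP, not earliest in the study window. If it means first ever recorded, patients recorded before 2010 drop out in every year and the drift is much smaller. This stands as an ambiguity. But WP1 is described as using 2010–2017 data, so earliest within those data is the more natural reading.
- **Unit.** The research question and the outcome both speak of patients, which fits one record per patient. This stands in part: the rule does not contradict the wording. But counting patients within a year does not require removing them from later years, and that removal is what makes the years unlike each other.
- **Level of detail.** A trend model, clustering and stratification may be left to a fuller document. This also stands, and no such omission is counted here. The record rule differs because the article states it, and states it for all of WP1.

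A reader might go further and infer that the window offers no valid comparator, or that the earlier cohort had different eligibility rules. The documents do not support this. The Introduction says "Since our earlier study there has been significant change in reperfusion strategies for STEMI in the UK" and that "we expected there to be an increase in the use of PHECG since our first report", which implies the earlier report as background, but the rollout is not dated and the earlier cohort's eligibility is not described. Nor do the documents commit the team to a rate pooled over STEMI and non-STEMI, or give the yearly shares needed to size a mix effect.

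**Conclusion.** The concern holds in a limited form. On the natural reading of the rule, the retained cohort loses repeat patients progressively, and the PHECG trend, a main outcome of WP1, is exposed to a change in case mix that the design itself creates.

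Under the assumed readmission rates and a 5 to 10 point lower PHECG use in repeat patients, the effect is a spurious rise of about 0.4 to 1.5 points over 2010–2017, against a 95% half-width of about 0.55 points. It could therefore be mistaken for, or hide, a small real change. It would matter little against a large one.

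Two stronger statements are tempting and should not be made. The first is that the trend is certainly biased upward: size and sign rest on a gap and a readmission rate that the documents do not give. The second is that the artefact exceeds sampling error throughout: its low end does not. The rule remains sound for mortality. This is a low-cost improvement to the trend analysis, not an error that undermines WP1.

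**What to change.** Limit the earliest-record rule to the mortality and reperfusion question. For the trend question, compute yearly PHECG proportions on all eligible EMS-attended ACS admissions, with standard errors clustered by patient. Every year is then formed in the same way, and the look-back artefact vanishes by construction.

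An alternative is the same fixed look-back for every year: drop a record only if the patient was admitted within a set period before it. With data from 2010 only, the first years would have to serve as run-in, so the all-admissions version is simpler.

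In either case, state whether earliest means earliest within 2010–2017 or first ever recorded in MINAP.

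The cost is a second analysis file from the same extract, provided the extract holds all of each patient's records. The two WP1 questions will then have different denominators, which the report should explain.
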